**Fig. 2 Fig2:**
[figure not shown]
Flow diagram to show the selection of health facility catchment areas

The participants in the trial will be women with disabilities, matched with women without disabilities from the same cluster. Participant eligibility will be determined based on the following inclusion criteria: (1) people who identify as women, aged 18–49 years (in this context we do not expect to find any trans men); (2) For women with disabilities, they must report ‘a lot of difficulty’ or ‘cannot do at all’ on any one or more of the six questions in the Washington Group short set or ‘daily’ and ‘a lot’ to additional questions on depression or anxiety from the enhanced question set [23]. The Washington Group questions were chosen as they are a widely used (in at least 75 countries to date), and internationally accepted measure of disability status for population-based surveys [24]; (3) Women without disabilities must be from the same cluster and aged within ± 5 years of the woman with disabilities. Participants will be excluded if they are not able to consent on their own as assessed by the Evaluation to Sign Consent Protocol (see next section)—with the exception of the process evaluation. For the process evaluation, those with severe cognitive or intellectual impairments (or their caregiver) may be included in order to get feedback from people with impairment types that might otherwise be excluded from the trial.

Health facility staff involved in the delivery of family planning services in the study area and intervention implementers will also be interviewed as part of the process evaluation to understand how the intervention was delivered and received.

### Who will take informed consent? {26a}

Informed consent will be sought for all participants before data collection. Potential participants will be provided with information about the research and study procedures by a trained interviewer, recruited by OPM Nigeria. They will have the opportunity to ask questions as part of the informed consent process. For in-person interviews, the information sheet will be either read aloud or given to the participant to read and written consent will be sought (signature or thumbprint if illiterate/blind).

All participants will be above the age of consent. Adults who lack capacity to consent on their own (e.g. people with severe intellectual/cognitive impairments) will be excluded. Capacity to consent for adults will be determined through the ‘Evaluation to Sign Consent’ [25], adapted specifically for the trial and asks four questions to gauge participant’s understanding (see supplementary materials, supplement 1). Participants that are unable to answer the questions even with repeating or re-explaining key parts of the information sheet will be excluded. During the process evaluation, participants that are unable to answer the Evaluation to Sign Consent questions (e.g. due to cognitive or intellectual impairments) may be included to ensure representation of different impairment types. If this is the case, their carer will be asked to complete the consent form, and if possible to still conduct an interview with the person with disabilities directly, they will obtain assent from the individual. Model consent forms can be provided on request.

### Additional consent provisions for collection and use of participant data and biological specimens {26b}

Participants are asked to consent to their anonymized data being shared in a public data repository. There are no consent provisions for biological specimens, as these will not be collected under this trial.

## Interventions

### Explanation for the choice of comparators {6b}

The comparator for the trial will be women in healthcare facility catchment areas receiving standard provision of family planning services. This was deemed a suitable choice for comparison with the intervention arm as it will enable the evaluation to determine if the intervention components of the IFPLAN project have any additional impact on access to family planning amongst women with disabilities compared to currently provided family planning services within the state. Women without disabilities are also included in order to determine whether the intervention has a specific effect amongst women with disabilities or a general effect for those with and without disabilities.

### Intervention description {11a}

The IFPLAN project aims to address multiple barriers to inclusion in family-planning services, using adaptive management and data to target and adjust programme components. The project comprises a range of national, state, and community and facility-based interventions of which this trial will only evaluate the community and facility-based interventions. However, this section describes the whole of IFPLAN so that the community and facility-based interventions can be understood within the entirety of the project.

The IFPLAN project consortium has developed a full theory of change for how the intervention package is anticipated to work (see supplementary materials, supplement 2), a simplified conceptual framework for which is shown in Fig. 3. This conceptual framework emphasizes how demand- and supply-side components of the project work together to increase access to modern contraception, in the context of efforts to change the structural conditions in which such decisions are made.

**Fig. 3 Fig3:**
[figure not shown]
Simplified conceptual framework for the programme. ***State and regional level activities (not evaluated by the trial)

The theory of change has three pathways. These are, broadly:Supporting the demand-side by increasing awareness, motivation, support from families/communities, and confidence to access family planning amongst women with disabilities;Supporting the supply-side by changing the service-provision to be more inclusive of persons with disabilities; andSupporting structural change by increasing engagement of OPDs in various aspects of the policy structure.

For each of the three pathways of the theory of change, as summarized in Fig. 3, a range of activities will be conducted to uphold people with disabilities’ rights to have control over their own bodies, fertility and sexuality. Pathway 1 is focused on demand-side changes, informed by a social and behaviour change (SBC) strategy to support people with disabilities to feel able, confident, motivated and supported if and when they choose to use modern contraceptives and practice family planning/child spacing. The SBC strategy has been developed based on existing literature and evidence in Nigeria [10, 12, 26–28], as well as formative research to determine current attitudes and behaviours in Kaduna city and using participatory approaches to define target audiences, and prioritize activities, messages and communication objectives.

The SBC activities include a weekly Hausa language radio drama, complemented by accessible digital and social media content, as well as interpersonal communication activities at the community level. These community-level activities will build on the characters and stories of the radio show, and digital and social media content, and include structured peer-to-peer sessions for people with disabilities to increase knowledge on SRHR and confidence in overcoming barriers to use services, if and when they need them, based on their own informed choices and bodily autonomy; household visits to people with disabilities and structured sessions with family members where needed; structured sessions with *Majalisa*s, existing community assemblies of male heads of households in Northern Nigeria to gain their engagement and support; town hall meetings to gain engagement and support from local leaders; and community plays to educate on SRHR and build on the stories from the radio drama.

The community-level activities will be led by inclusive community-based champions who are trained by Sightsavers and supported by local OPDs. Activities in the structured sessions and town hall meetings will be aided by facilitation guides and content will include (a) the use of an audio device for group listening to radio stories and discussion sessions; (b) the use of a board game to engage young people in the messages, myths and benefits of family planning (adapted from MSI Reproductive Choices to be disability inclusive and suitable for the Nigerian context); and (c) printed materials to aid discussions, such as flip charts and information booklets for young girls, women and men. Prior to implementation, pre-testing of all the materials used in these sessions was conducted with people in two different communities in Kaduna representing a range of impairment types, and focused on the acceptability of the materials.

For supply-side changes under pathway 2, these will be targeted predominantly at primary public health facilities offering family planning services (although secondary and tertiary health facilities, as well as private providers will be included), and focus on three key areas: (1) accessibility audits of and improvements to family planning facilities; (2) disability inclusive training of service providers based on training needs assessments for each health worker cadre, with training conducted by representatives from local OPDs; and (3) participatory scorecard assessments developed by people with disabilities, service providers and decision-makers based on Sightsavers’ Disability Inclusive Scorecard (DISC) tool [29]. DISC is a rights-based tool, aligned with the United Nations Convention on the Rights of Persons with Disabilities (UNCRPD), and brings together people with disabilities, service providers, and local administration to develop and assess indicators to determine the quality of services provided to people with disabilities, collaboratively identifying key gaps and actions required to improve access to family planning for people with disabilities at facility level.

Finally, for structural changes under pathway 3, activities will be focused around capacity building of OPDs, advocacy for inclusive SRHR, and representation of OPDs in healthcare committees.

Interventions under pathway 1 and pathway 2 should increase demand and supply, respectively, and as such increase access to family planning. Pathway 3 is expected to facilitate an increase in access by changing the structures in which demand and supply are met. Pathways 1 and 2 will include activities targeted at the health facilities and health facility catchment areas in the intervention clusters, whereas the activities under pathway 3, as well as some of the activities under pathway 1 (radio, digital, and social media content) will have a broader geographical focus, operating at the state or regional levels. Consequently, this cluster randomized controlled trial will only focus on community and facility-based activities under pathways 1 and 2. Although state- and regional-level activities will be part of the implementation of the IFPLAN project, these will not be part of the evaluation as there will be no means of preventing contamination of the control clusters.

### Criteria for discontinuing or modifying allocated interventions {11b}

Funds may not permit project implementation in all health facilities within the intervention cluster.

### Strategies to improve adherence to interventions {11c}

Intervention implementation will be monitored and an adaptive management approach adopted by the implementing partners to ensure intervention delivery is contextually appropriate and achieves the desired goals of the project [30].

### Relevant concomitant care permitted or prohibited during the trial {11d}

No restrictions on concomitant care.

### Provisions for post-trial care {30}

No specific provisions for post-trial care.

### Outcomes {12}

The primary outcome for the trial, as shown in Table 2, is access to modern family-planning methods. We will also measure ‘realized access’, or *use*, as an important secondary outcome, defined as women aged 18–49 with disability who are sexually active and would like to delay or reduce future pregnancies and are using modern family-planning methods to achieve this.

**Table 2 Tab2:** Summary of outcomes for the IFPLAN project’s cluster randomized controlled trial

	**Outcome name**	**Measure**
**Primary outcome**	Access to family planning	Survey: binary (yes / no), based on composite of questions: • Know of at least three modern contraceptive methods that are available; & • Know where to access modern family-planning; & name the location; & list the available family planning services; & • Believe that they could use services if they needed them
**Secondary outcome**	Knowledge of family planning	Survey: binary (yes / no), based on composite of questions: • Know of at least three modern contraceptive methods that are available
	Intention to use	Survey: binary (yes / no), based on: • Will use contraceptive method in the future
	Use of family planning (modern method)	Survey: binary (yes / no), based on composite of questions: • Participant or participant’s partner currently doing something or using any method to delay or avoid getting pregnant; & • (Using a modern contraceptive method)
	Unmet need for family planning	Survey: binary (yes / no), based on composite of questions: • Would prefer to delay or not to have another child & • Not using contraception
	Perceived attitudes towards women with disabilities	• Score based on inclusion and participation module of survey

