## Discussion

There is currently a dearth of information regarding effective interventions for inclusive access to sexual and reproductive health services for women with disabilities in LMICs [7]. However, defining access to services is complex, as it is not a single variable that can be measured directly [18]. Use of services is not equivalent to access, since (1) not everyone has an objective ‘need’ for services and (2) not everyone who has a need has a desire—or subjective ‘need’—to use services. For family planning, we might define objective need, (1), as fecund women who report that they would like to delay or permanently end having children while also having sexual relations with a fertile man. This raises a secondary issue, which is that this ‘objective’ need is based on the *subjective* desires that the woman has regarding family planning. Unlike for a condition that can be objectively assessed—such as HIV status—the need for family planning has only subjective components, both in determining that there is an issue that could be remedied with use of services, (1), and the desire to use services to address this need (2). Use is therefore realized access [18]. Unlike HIV, there is no comparable ‘treatment cascade’ either, since for any position on a cascade there is a reasonable choice, for example between having more children or not. In the context of persons with disability, this is particularly important when considering the position of women with disability who might be pressured into considering contraceptive methods against their will [36]. A further complication is that a woman’s desires for family-planning services can change over time, and so it is not possible to use her position at baseline as a guide to what ‘should’ be her position at endline.

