Access is made up of several supply- and demand-side factors [18], with additional factors that affect only persons with disability [3, 4]. A complete assessment of access could ascertain whether someone who had a need and desire for service would be able to use them. However, this would only be successful if our model was correct, which for persons with disability, and many possible impairments, is unlikely. If the model is not correct then, for example, we might say that someone ‘has access’ to services when, in fact, there remained impediments (or lack of support factors) that would render the services inaccessible. If some of the impediments have been removed, then we could say her access has ‘improved’, while being aware that access has not been realized.

We have conceptualized ‘access to family planning’ for the purposes of this trial as shown in Table 2, to try to address these issues. This conceptualization takes account of the following characteristics of access in the context of this family-planning intervention:All women should know about available services if they are to have ‘access’;Women who want to delay or reduce future pregnancies should be able to realize ‘access’ through use of services;Women who do not want to delay or reduce future pregnancies, or are not in sexually active relationships, are not expected to have realized their ‘access’ to services through service use; instead, understanding access is a composite of their beliefs about using services if they needed them (hypothetically) and their impressions of the barriers or facilitators that we expect should determine use.

There remains a challenge with this conceptualization. Part of the effects of the intervention could be to increase voluntary demand for family planning, leading to an increase in the number of women who would like to delay or reduce future pregnancies. This might occur without a compensatory increase in the availability of services since the intervention has only limited influence over the provision of services. Demand will be included as a secondary outcome in anticipation of this eventuality.

Despite the challenges in measuring access, it is hoped that the evidence generated by this trial strengthens the evidence base on how to improve inclusive family planning for women with disabilities in Nigeria and other LMIC settings.

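### Unmet need, use and demand are defined inconsistently within the protocol, and the unmet-need rule as written dilutes the ratio for research question 3

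*Protocol article*

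**What the plan says.** **Use.** The text of Outcomes {12} describes use, or realised access, as disabled women "who are sexually active and would like to delay or reduce future pregnancies and are using modern family-planning methods to achieve this". In the same section, Table 2 has two conditions: the woman or her partner is "currently doing something or using any method to delay or avoid getting pregnant", and the method is modern. It has no separate item on sexual activity or fertility preference. Neither place states a denominator.

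**Unmet need.** Table 2 has two items. The first is "Would prefer to delay or not to have another child"; the second is that no contraception is being used, of any type. The Discussion describes objective need, tentatively, as "fecund women who report that they would like to delay or permanently end having children while also having sexual relations with a fertile man". It adds that women outside sexually active relationships are not expected to show access by using services.

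**Demand.** The Discussion warns that the intervention could raise voluntary demand, "leading to an increase in the number of women who would like to delay or reduce future pregnancies", and states: "Demand will be included as a secondary outcome in anticipation of this eventuality". Table 1 lists knowledge, unmet need and use as secondary outcomes. Table 2 adds intention to use and perceived attitudes. Neither has a demand row.

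Research questions 2 and 3 (Objectives {7}) concern use and unmet need respectively.

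**The concern.** Two of the three research questions rest on outcomes whose rules differ between parts of the same article.

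- For unmet need, Table 2 can be applied exactly as it stands. It then classifies as unmet need women whom the Discussion would not regard as in need: those who are not sexually active and those who are not fecund. The intervention cannot resolve a need these women do not have, so they pull a ratio measure towards 1.
- For use, the text leaves open whether its extra conditions describe who counts as a user or who is analysed. Under the second reading, women would be selected on a wish that the Discussion says the intervention may change.
- Without a demand outcome, a rise in use or unmet need caused only by more women wishing to delay cannot be told apart, among the listed outcomes, from a change in how well that wish is met.

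The Blinding section says the data analyst will not be blinded, which is a further reason to settle each rule before endline results are seen.

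**Working it through.** The plan gives no expected figure for use, unmet need or demand, and its sample size concerns only the primary outcome. There is therefore no stated number to reproduce. The check compares the definitions and then sizes the effect with assumed inputs.

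**1. Definitions side by side**

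- *Use.* Text: sexually active, wants to delay or reduce pregnancies, and uses a modern method. Table 2: currently doing something to avoid or delay pregnancy, and the method is modern. The Table 2 purpose clause largely implies the wish. Over all women, the two numerators should therefore nearly coincide.
- *Unmet need.* Discussion: fecund, wants to delay or end childbearing, and in a sexual relationship with a fertile man. Table 2: wants to delay or stop, and not using contraception. Fecundity and sexual relations are missing from Table 2.
- *Method type.* Use requires a modern method; unmet need requires no method at all. A woman who wants to delay and uses a traditional method counts in neither outcome.
- *Demand.* Promised in the Discussion, absent from both tables. The nearest row, intention to use, asks about future contraceptive use, not about wanting fewer or later pregnancies.

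**2. Dilution of unmet need**

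Assumed inputs: true unmet need of 25% in control and 20% in intervention, plus a proportion *w* of all women in each arm who are counted as unmet need without being at risk, and who do not change.

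True RR = 0.20 / 0.25 = 0.80. Observed RR = (0.20 + *w*) / (0.25 + *w*).

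- *w* = 0.10: 0.30 / 0.35 = 0.857
- *w* = 0.15: 0.35 / 0.40 = 0.875
- *w* = 0.20: 0.40 / 0.45 = 0.889

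The planned model is logistic, so the odds ratio is also relevant. Ignoring clustering, the true OR = (0.20/0.80) / (0.25/0.75) = 0.75. At *w* = 0.15, the observed OR = (0.35/0.65) / (0.40/0.60) = 0.81. The absolute difference stays at 5 percentage points throughout.

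The same point can be put as a share *a* of the women counted as unmet need. With a true RR of 0.75, observed RR = *a* + (1 − *a*) × 0.75. This gives 0.775 at *a* = 0.10 and 0.875 at *a* = 0.50 (assumed range).

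**3. A shift in demand alone**

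Assumed inputs: the proportion wanting to delay is 40% in control and 50% in intervention; 30% of those women use a modern method in both arms, and the rest use nothing.

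- Use over all women: 0.40 × 0.30 = 12% versus 0.50 × 0.30 = 15%; RR = 1.25.
- Use among women in demand: 30% versus 30%; RR = 1.00.
- Unmet need over all women: 0.40 × 0.70 = 28% versus 0.50 × 0.70 = 35%; RR = 1.25.

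The denominator therefore matters for use. An all-women analysis of unmet need will also show an apparent worsening when demand rises, even with a corrected numerator.

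**The case against.** The strongest reply is that these are wording gaps in secondary outcomes, in an article that summarises a fuller protocol. Its parts carry different weight.

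- *Use reads naturally as a numerator.* This stands. The text lists the features of a woman who counts as a user, and nothing in the statistical methods restricts the analysed women. A reader might infer that the plan selects women on a post-randomisation wish and that a real gain would vanish (1.25 becoming 1.00). The document does not say so. That result follows only if the text is taken as a denominator, which is left open.
- *The account of need in the Discussion is tentative and is not an endpoint definition.* This is correct, so the mismatch is with the protocol's own reasoning, not with a second fixed rule. But the Table 2 rule is stated, not left for later, and as stated it includes women who are not at risk.
- *Any-method non-use is legitimate.* This stands. The project aim attaches modern methods to access, and does not qualify unmet need in that way. A reader might infer that unmet need must be based on modern methods, or that all pregnant women must be coded as having none. The documents support neither; both are choices to be stated.
- *Intention to use may be the intended demand measure.* Possible, but the article does not say so, and the item asks something different. Nor does the missing row alter which women are analysed; it affects interpretation only.
- *The magnitudes are assumed.* True. They show direction and plausible size, not an estimate for Kaduna.

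**Conclusion.** The inconsistencies are real and lie within one document. The firmest is unmet need: applied as written, Table 2 includes women who are not sexually active or not fecund and so dilutes the ratio for research question 3. With 10% to 20% of women miscoded equally in both arms (assumed), a true RR of 0.80 appears as 0.857 to 0.889, while the risk difference is unchanged. For use, the conflict is an ambiguity: minor under the numerator reading, material only under a restricted denominator. For demand, a promised outcome is missing from both outcome tables, and with it the means of interpreting the other two.

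It would go too far to conclude that research questions 2 and 3 will be answered on the wrong women. The document does not fix a restricted analysis population, and the data needed for either version are to be collected. The primary outcome, its sample size and the randomisation are untouched. Severity is moderate.

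**What to change.** Before endline data are analysed, give each outcome one numerator and one denominator:

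- **Use:** current modern-method use (the Table 2 rule), with all enrolled women in the denominator for the arm comparison, within each disability group. Align the text in Outcomes {12}, and report the proportion among sexually active women who want to delay as descriptive only.
- **Unmet need:** add sexually active and fecund to the two Table 2 items, and code all other enrolled women as no. State explicitly how pregnant women and users of traditional methods are coded.
- **Demand:** add a row to Tables 1 and 2 (wants to delay or stop, all enrolled women). It should be read alongside use and unmet need, because rising demand will still raise unmet need over all women.

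The cost is wording, derivation code and a recorded amendment. Table 3 shows the marriage and sexual activity, fertility preference, reproductive history and contraceptive use modules at both surveys, so no new module is needed. The downside is a lower unmet-need prevalence: in the illustration above, 25% instead of 40% in the control arm.
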